### Statistical analysis

A two-sided *p*<0.05 is set as a statistical difference. Pearson χ^2^ or Fisher’s exact test and Student t test are performed for the comparison of baseline characteristics, perioperative outcomes and the pulmonary functions. Comparisons of OS and RFS between minimally invasive segmentectomy and lobectomy groups are all estimated by Kaplan-Meier method and testified by the two-side Log-rank test. Cox proportional hazard regression model will be used to evaluate the hazard ratio of minimally invasive segmentectomy group and minimally invasive lobectomy group for OS and RFS, respectively. Subgroup analyses will also be performed by total lesion size ≤ 2cm or 2cm-≤3cm. Intention to treat analysis (ITT) will be performed for all enrolled patients. Per protocol analysis (PP) will be performed for patients who have completed the trial in compliance with the protocol.

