### Inclusion criteria

Patients will be eligible if they fulfill all the following inclusion criteria. (1) Patient age is between 20 and 80 years old; (2) The location of the primary lesion should be in the peripheral 1/3 pulmonary field, where both lobectomy and segmentectomy with satisfactory proximal margin can be achieved; (3) Segmentectomy includes combined segmentectomy, but the extent of segmentectomy should be <1/2 of the corresponding lobe; (4) The primary lesion should appear as GGO containing on thin-sliced CT scan. Maximum size of the lesion should >0.5cm and ≤3cm, with the solid component size >0.5cm but ≤2cm on lung window (corresponding to cT1a-b); (5) Patients with ipsilateral multiple nodules can be included only if there are no more than 2 additional GGOs in a different lobe from the primary lesion, and must be peripherally located that can be removed by wedge resection. If the secondary lesion is a pure GGO, the size should be <1cm. If the secondary lesion is a mixed GGO, the solid component size should be <0.5cm. At most two wedge resections are allowed during the simultaneous operation for the primary lesion; (6) Patients with contralateral lesions can also be included if there are ≤3 GGO-containing lesions, with a solid component size smaller than that in the primary lesion; (7) All patients should be functionally fit for standard lobectomy and segmentectomy, with an American Society of Anesthesiologists (ASA) score of I-III and spirometry results of FEV1 ≥1.2L, FEV1% ≥60%, DLCO% ≥60%;(8) All patients are voluntary to participate in this clinical trial and written informed consents should be signed (**Table 1**).

**Table 1 T1:** Patient inclusion and exclusion criteria.

Inclusion criteria
1. Age between 20 and 80 years old;
2. Lesion locates in the peripheral 1/3 pulmonary field, and both lobectomy and segmentectomy (satisfied margin) can be done;
3. Segmentectomy includes combined segmentectomy, but the extent of segmentectomy should <1/2 of the lobe;
4. The primary lesion should appear as GGO containing on thin-sliced CT scan. Maximum size of the lesion should >0.5cm and ≤3cm, with the solid component size >0.5cm but ≤2cm on lung window;

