### Preoperative examinations

Once the candidate is qualified, the informed consent will be signed. The baseline characteristics of all the candidates, including family history, smoking history, comorbidity, symptoms and signs, would be collected. Before surgery, those qualified patients will take full preoperative examinations and evaluations, including chest CT, abdominal CT or ultrasound, cervical ultrasound examinations. Head magnetic resonance imaging (MRI) and positron emission tomography/computed tomography (PET.CT) are also preferred for the prevention of cancer metastasis, especially for patients with clinical T1b NSCLCs. Besides, preoperative pulmonary function examination as well as serum tumor markers will also be tested before surgery. In addition, each patient will receive simplified bedside pulmonary function examination the day before operation. All the preoperative examination and evaluation data will be entered into an investigator initiated trial Electronic Data Capture (IIT-EDC) System (Taimei Technology, Zhejiang Province, China) an electronic data collection system.

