### Study endpoints

The primary endpoint is 5-year recurrence-free survival (RFS), calculated from the date of surgery to the date of cancer recurrence or patient death or the last follow-up. The secondary endpoints are 5-year overall survival (OS), perioperative outcomes and pulmonary function preservation. OS is calculated from the date of surgical resection to the date of patient death or the last follow-up. Perioperative outcomes include blood loss, operation time, morbidity rate, mortality rate, chest drain duration, length of hospital stay, and residual lung re-expansion. Pulmonary function change will be evaluated on short-term (the second day after surgical operation) and on long-term (6 month after operation) after surgery. 5% difference in FEV1 at 6 months after surgery is set as the secondary end point between the segmentectomy and the lobectomy groups. Exploratory research includes prediction of histological subtypes on preoperative imaging using artificial intelligence (AI). We also try to explore the characteristics of gene mutation status *via* next-generation sequencing (NGS) among GGO-containing early-stage NSCLCs.

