Apart from the differences in inclusion criteria, the surgery approach and resection extent are different in this designed trial. No surgical approach was specified in either CALGB 140503 and JCOG 0802, which means that minimally invasive and open surgery can all be used (15, 16). Thoracic surgery has come into the era of minimally invasive surgery, which helps to reduce surgical trauma and function loss compared with traditional open thoracotomy. So, in this trial, the surgical approach is limited to minimally invasive surgery. The extent of pulmonary resection has now become the dominant factor on surgical risks and functional recovery. Unlike the sublobar group of CALGB 140503, which did not distinguish between wedge resection and segmentectomy, patients in JCOG 0802 were only divided into segmentectomy group and lobectomy group. While in JCOG 0802, there was no restriction on number of segments resected in the segmentectomy group. Segmentectomy in the GREAT study must be less than 1/2 of the corresponding lobe. If the number of segments removed ≥1/2 of the total segments of corresponding lobe, the patients will be withdrawn from the study.

Theoretically, when less lung tissue is removed, more lung function may be retained. However, pulmonary function preservation has failed to reach the expected level of 10% in the JCOG 0802 trial (16). From our previous study, if the number of segments removed ≥1/2 of the total segments of corresponding lobe, then the lung function loss of segmentectomy is similar to that of lobectomy (18). And in this previous observational study, VATS segmentectomy could reserve about 4-5% more FEV1 than corresponding VATS lobectomy. So, in the GREAT trial, segmentectomy is expected to have 5% less FEV1 loss than lobectomy.

Only with such evidences can early-stage lung cancer patients truly benefit from the advent of modern surgical techniques.

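### FEV1 is compared by an unadjusted t test although every patient has baseline spirometry; baseline-adjusted ANCOVA would give a modest, nearly free gain in precision

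*Protocol article*

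**What the plan says.** The Statistical analysis section covers baseline characteristics, perioperative outcomes and lung function in one sentence: besides the chi-squared or Fisher test for proportions, "Student t test are performed for the comparison of baseline characteristics, perioperative outcomes and the pulmonary functions". It names a regression model (Cox) only for OS and RFS.

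Under Study endpoints, the FEV1 endpoint is worded in two ways. One sentence says "Pulmonary function change will be evaluated on short-term" and on long-term follow-up, meaning POD2 and 6 months. The other says "5% difference in FEV1 at 6 months after surgery is set as the secondary end point between the segmentectomy and the lobectomy groups". The Discussion gives the expectation as a difference in loss: "segmentectomy is expected to have 5% less FEV1 loss than lobectomy".

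Baseline values exist for both time points:
- **For 6 months:** the Inclusion criteria require "spirometry results of FEV1 ≥1.2L, FEV1% ≥60%, DLCO% ≥60"%, and Preoperative examinations adds that "preoperative pulmonary function examination as well as serum tumor markers will also be tested before surgery". The Follow-up section repeats spirometry in each participant at 6 months.
- **For POD2:** "each patient will receive simplified bedside pulmonary function examination the day before operation", and Postoperative managements repeats the test on POD2.

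**The concern.** The Conclusions make better lung function, better perioperative outcomes, or both a condition for calling segmentectomy the preferred procedure. The expected FEV1 effect is small: 5% in this trial, after 4-5% in the sponsor's earlier observational study. How precisely that difference is estimated therefore matters.

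A patient's FEV1 before surgery should predict FEV1 at 6 months well. A t test on 6-month values ignores that information. A t test on change uses it, but with the coefficient fixed at 1 instead of estimated from the data. In either case some chance imbalance in baseline FEV1 stays in the estimate. ANCOVA removes its linear part and narrows the confidence interval, using data that are already collected.

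**Working it through.** **Figures in the plan.** There is no sample size, SD or power for FEV1 to reproduce. The only sample size, 1024, is set by 5-year RFS and is used here only for the number per arm: 1024 × 0.95 / 2 ≈ 486 after the stated 5% drop-out.

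**Assumptions (not in the documents).** The correlation ρ between pre-operative and 6-month FEV1, and the SD of FEV1 in percentage points. The SD is taken as equal before and after surgery.

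**Variance of the arm difference**, in units of 2·SD²/n with n per arm:
- t test on the 6-month value: 1
- t test on change: 2(1 − ρ)
- ANCOVA: 1 − ρ²

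The ratio of ANCOVA to the raw-value t test is therefore 1 − ρ². The ratio to the change-score t test is (1 − ρ²) / [2(1 − ρ)] = (1 + ρ)/2. The reduction in standard error is 1 minus the square root of the ratio.

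| ρ | Ratio to t test on change | SE smaller by | Ratio to t test on raw value | SE smaller by |
|---|---|---|---|---|
| 0.5 | 0.75 | 13% | 0.75 | 13% |
| 0.7 | 0.85 | 8% | 0.51 | 29% |
| 0.8 | 0.90 | 5% | 0.36 | 40% |
| 0.9 | 0.95 | 2.5% | 0.19 | 56% |

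**Confidence interval, SD 20 and ρ 0.7.** The SE on raw values is 20 × √(2/486) = 1.283, so the 95% half-width is 1.96 × 1.283 = 2.51 points. On change it is 2.51 × √0.6 = 1.95. With ANCOVA it is 2.51 × √0.51 = 1.80.

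**Power for a 5-point difference**, two-sided 5%, 486 per arm:

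| SD, ρ | t test on raw value | t test on change | ANCOVA |
|---|---|---|---|
| 20, 0.7 | 97.4% | 99.9% | >99.9% |
| 25, 0.5 | 87.7% | 87.7% | 95.0% |
| 30, 0.7 | 73.8% | 91.8% | 95.3% |

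**Chance imbalance.** At SD 20 the SE of the baseline difference between arms is also 1.28 points. With ρ = 0.7, an imbalance of that size shifts the change-score estimate by (1 − 0.7) × 1.28 ≈ 0.4 points and the raw-value estimate by 0.7 × 1.28 ≈ 0.9 points. The interval already allows for this random error.

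**Simulation check** (3000 trials per ρ, SD 15, 486 per arm). Empirical SEs for raw, change and ANCOVA were 0.957, 0.731 and 0.680 at ρ 0.7, and 0.963, 0.447 and 0.435 at ρ 0.9. All three estimators were unbiased, with mean error below 0.02 points. ANCOVA was the most precise at every ρ tried (0.5, 0.7, 0.8, 0.9).

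**The case against.** A t test on change is an accepted analysis of a randomised trial, and the article's wording points to change or loss. On that reading the baseline is already used, the gain is a few percent of the standard error, and power for 5 points is high unless the SD is large. The article is also condensed, and an analysis plan that is not shown may add covariates.

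Most of this stands, and it limits the point. It does not remove it: the article names a specific test for lung function, so the matter is a stated choice and not a missing detail, and a method at least as precise is available from data in hand.

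Two objections narrow the remedy. First, the article leaves the scale of the 5% target open. The ratio (1 + ρ)/2 holds for absolute change with equal SDs and does not carry over directly to percent loss, and an adjusted difference in litres would not answer a percentage target. Second, the pre-operative bedside test and randomisation are both set for the day before surgery in an open-label trial, and the article does not say which comes first. The bedside value may therefore have been measured after allocation. The eligibility spirometry does not have this problem.

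A reader might infer more than the documents support:
- **That the t test is biased or invalid.** It is neither, because allocation is randomised.
- **That the plan wastes half or more of its information.** The 49-81% figure needs a comparison of raw 6-month values, which is not the likelier reading.
- **That adjusting for lobe brings a further known gain.** The article gives no figure for how FEV1 loss varies by lobe.

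**Conclusion.** The point holds as a modest gain in efficiency on a secondary endpoint. Against a t test on change, ANCOVA reduces the variance by about 5-15%, or the standard error by about 2.5-8%, for ρ from 0.9 down to 0.7. At SD 20 and ρ 0.7 the 95% half-width falls from 1.95 to 1.80 points. If raw 6-month values were compared, the variance reduction would be 49-81%.

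These sizes rest on an assumed SD and correlation and on equal SDs before and after surgery. That ANCOVA is at least as precise does not depend on those particular values in a 1:1 trial of this size. The benefit is a narrower interval and protection against chance baseline imbalance. Nothing here shows that the FEV1 conclusion would change, and the RFS analysis and the sample size of 1024 are untouched.

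**What to change.** Replace the t test for lung function in the Statistical analysis section with wording to this effect:

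- **6-month FEV1:** ANCOVA with arm and pre-operative (eligibility) FEV1. State the scale in which the 5% target is expressed and fit the model on that scale. Report the adjusted difference with its 95% CI.
- **Lobe of the primary lesion:** may be added, since it is known before randomisation; claim no gain for it.
- **POD2 bedside measure:** the same model with its own pre-operative value, only where that value was taken before allocation. Confirm the order from the recorded times.
- **t test:** keep it as a sensitivity analysis.

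The cost is a few lines of text and one degree of freedom out of about 970. Lobe would take three more, as the right middle lobe is excluded and four lobes remain. No new measurement is needed.

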**Methods/design:**

Sample sizes are 1024 patients, who will be randomized into minimally invasive segmentectomy and lobectomy groups . Patients will be collected from 19 hospitals in China. Patients with peripheral mixed ground glass opacity (mGGO) with 0.5cm<total lesion size ≤ 3cm and 0.5cm<solid component size ≤ 2cm in lung window on CT scan are enrolled. The primary endpoint is 5-year recurrence-free survival (RFS). The secondary endpoints are 5-year overall survival (OS), perioperative outcomes and pulmonary function preservation. Kaplan-Meier curves are plotted to compare the survival outcomes between the two arms. Subgroup analyses are also performed to investigate the benefit of segmentectomy among different clinical variables.

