### Randomization

Central randomization will be performed and the patients will be randomized in a 1:1 ratio to either a minimally invasive anatomical segmentectomy group or a minimally invasive lobectomy group. Randomization will take place the day before surgery through a Central Randomization System based on the IIT-EDC.

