### Surgery

Minimally invasive thoracic surgery including both VATS and RATS is required for this trial, including single-port, two-port, three-port or four-port incisions without rib spreading. Lobectomy and segmentectomy should be anatomically resected. The hilar structures should be separated and pulmonary vessels and bronchus should be divided respectively. Lobar fissure and intersegmental plane should be managed either by stapler alone or by stapler together with energy devices. Both segmentectomy and lobectomy groups should receive systemic lymph node dissection or sampling according to the NCCN guidelines (5).

Intraoperative frozen pathology is required for the resected specimen, including the pulmonary surgical margin of segmentectomy. If the segmental resection margin is positive of malignancy on frozen section, segmentectomy should be converted to lobectomy. All the intraoperative data including intraoperative complications will be carefully recorded. In addition, preoperative imaging, peripheral blood sample and intraoperative tumor specimen of each patient will also be collected for further exploratory research (**Figure 1**).

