### Sample size calculation

Expected 5-year RFS is 91% according to a previous study at Shanghai Chest Hospital (6). With a one-sided alpha error of 5% and at least 80% power and a non-inferiority margin of 5% along with a drop-out rate of 5%, the sample size of this study requires 1024 patients.

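### The continuous perioperative outcomes from 19 hospitals are assigned an unadjusted t test, which is valid but gives up some precision that a hospital term would recover

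*Protocol article*

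**What the plan says.** The abstract states the multicentre setting: "Patients will be collected from 19 hospitals in China". The Study endpoints section lists the outcomes at issue: "Perioperative outcomes include blood loss, operation time, morbidity rate, mortality rate, chest drain duration, length of hospital stay, and residual lung re-expansion". Five of these are continuous (blood loss, operation time, drain duration, hospital stay, re-expansion) and two are binary (morbidity, mortality).

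For all of them the Statistical analysis section names Pearson chi-square or Fisher's exact test, and "Student t test are performed for the comparison of baseline characteristics, perioperative outcomes and the pulmonary functions". The threshold is a two-sided p below 0.05. No hospital term, stratum or covariate is mentioned for these comparisons anywhere in the article.

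The Randomization section says that "the patients will be randomized in a 1:1 ratio" and that "Randomization will take place the day before surgery through a Central Randomization System based on the IIT-EDC". It names no stratification factor, so hospital is neither included nor ruled out.

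The Surgery section allows video-assisted or robotic operation, "including single-port, two-port, three-port or four-port incisions without rib spreading", stapler with or without energy devices, and nodal dissection or sampling. The Postoperative managements section prefers digital drainage but does not require it.

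**The concern.** A two-sample t test has no place for hospital. Where hospitals differ in how they operate and drain, part of the spread in operation time, blood loss, drain duration, stay and re-expansion is between hospitals. The t test counts that spread as noise. Hospital is known for every patient before randomisation, so a model could remove it at little cost.

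The stake is precision on a secondary endpoint that the authors intend to use. The Discussions part of the abstract and the Conclusions make better perioperative outcomes one of two and/or routes, next to pulmonary function, to calling segmentectomy the preferred procedure. That step comes only after the primary endpoint has been met and overall survival has been shown non-inferior. The trial is sized for recurrence-free survival alone, so no power is stated for the perioperative comparisons.

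**Working it through.** **Inputs from the article.** 19 hospitals; 1024 patients, 1:1, hence 512 per arm; two-sided alpha 0.05 for these comparisons; no stratification factor named.

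**Input that must be assumed.** The between-hospital share of variance (intraclass correlation, ICC) is not given. The range used is 0.01 to 0.30.

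**The plan's own figure.** The only design figure is "the sample size of this study requires 1024 patients", which concerns recurrence-free survival. With 91% against 86% at five years, HR = ln(0.86)/ln(0.91) = 1.599. Schoenfeld's formula at one-sided 5% and 80% power gives 113 events. Then 113/0.115 = 983, and 983/0.95 = 1035, about 1% above 1024. The article does not name its formula, and a non-inferiority comparison of two proportions would need only 855. Either way the figure says nothing about the perioperative outcomes.

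**Step 1, reference effect.** The t test has 80% power for a difference of (1.960 + 0.842) × sqrt(2/512) = 0.175 SD. No perioperative effect size is stated, so this is only a yardstick.

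**Step 2, effect of a hospital term.** Adjustment removes the between-hospital part, so the residual variance is (1 − ICC) times the total. The unadjusted standard error is therefore larger by a factor 1/sqrt(1 − ICC). Power after adjustment is Φ(2.80/sqrt(1 − ICC) − 1.96). The t test on 1024 patients performs like an adjusted analysis of 1024 × (1 − ICC).

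| Assumed ICC | Unadjusted SE larger by | Adjusted power (80% unadjusted) | Equivalent adjusted N |
|---|---|---|---|
| 0.01 | 0.5% | 80% | 1014 |
| 0.02 | 1.0% | 81% | 1004 |
| 0.05 | 2.6% | 82% | 973 |
| 0.10 | 5.4% | 84% | 922 |
| 0.20 | 11.8% | 88% | 819 |
| 0.30 | 19.5% | 92% | 717 |

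**Step 3, cost of the hospital term.** Nineteen hospitals use 18 degrees of freedom. If allocation is not balanced by hospital, the adjusted variance is multiplied by about 1 + 18/1003 = 1.018. Adjustment then breaks even at ICC = 1 − 1/1.018, about 0.018. With this factor, power is about 80% at ICC 0.01 and 0.02, 81% at 0.05, 83% at 0.10, 87% at 0.20 and 91% at 0.30.

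**Step 4, false-positive rate of the planned t test.** If allocation is not balanced by hospital, the rate stays nominal. Simulation with 19 hospitals of uneven size and 3000 runs per setting gave 5.2%, 5.1% and 5.3% at ICC 0.10, 0.20 and 0.30. If allocation is balanced by hospital, the closed form 2 × [1 − Φ(1.96/sqrt(1 − ICC))] gives 3.9%, 2.8% and 1.9%, and the same simulation gave 4.0%, 3.5% and 1.9%. The simulated SE ratios under balanced allocation (1.05, 1.11 and 1.18) were close to, and slightly below, the closed form.

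**Step 5, binary outcomes.** Assume 15% morbidity with a between-hospital SD of 5 percentage points. The ICC is 0.05²/(0.15 × 0.85) = 0.02 and the SE penalty is about 1%. For rare deaths it is practically nil.

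**The case against.** The strongest reply is that nothing here is an error. An unadjusted test of randomised arms is valid, the article does not contradict itself, and the treatment of centre effects is often left to an analysis plan, which is not shown. Validity is conceded. The last part stands less well, because the article does not stay silent: it names the test, and that test has no room for hospital.

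A second reply is that the gain may be trivial. No ICC is given, no clinically relevant perioperative difference is stated, and the t test already has 80% power for about 0.175 SD. At an ICC of 0.02 or less, adjustment buys nothing worth having. This stands, and it is why the low end of the range has to be shown. The text on approach, ports, energy devices and drainage makes variation between hospitals plausible but does not give its size.

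A reader might also infer three stronger things:

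- **Inflated false positives or bias.** Not supported. The planned test is at its nominal level or below it.
- **A conservative test as a matter of fact.** That requires allocation balanced by hospital, and the Randomization section does not say so.
- **The same weakness in the chi-square and Fisher tests.** Step 5 shows almost nothing to gain for morbidity or mortality.

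**Conclusion.** The point holds as a minor efficiency improvement for the five continuous perioperative outcomes. The fixed t test is valid, or conservative under hospital-balanced allocation. Its standard error exceeds that of a hospital-adjusted analysis by about 0.5% to 20% over an assumed ICC of 0.01 to 0.30. The gain is negligible up to about 0.02, roughly 2 power points at 0.05, and material from about 0.10. These sizes rest wholly on the assumed ICC and on a hypothetical 80%-power comparison.

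It would be tempting to conclude that the case for segmentectomy as the preferred procedure is at risk. The documents do not support that: perioperative benefit is one of two alternative routes to a secondary conclusion, and the recurrence-free survival non-inferiority conclusion does not depend on these tests.

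**What to change.** In the Statistical analysis section, replace the Student t test for operation time, blood loss, chest drain duration, length of stay and re-expansion with a linear model containing arm and hospital, as a fixed or random effect. State in advance how very small hospitals are pooled. Report the adjusted mean difference with its 95% confidence interval. Keep the planned chi-square or Fisher tests for morbidity and mortality.

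The cost is one sentence, a pooling rule and about 18 degrees of freedom out of roughly 1000. No additional data are needed, since each patient's hospital is known before randomisation. The change should be made before these outcomes are analysed.

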**Discussions:**

If the primary endpoint shows at least non-inferiority in 5-year RFS of segmentectomy to lobectomy, minimally invasive segmentectomy can be recommended as an alternative to minimally invasive lobectomy. If second endpoints show non-inferior 5-year OS along with better perioperative outcomes and/or better pulmonary function preservation of segmentectomy compared with lobectomy after the primary endpoint has reached, minimally invasive segmentectomy may become a preferred procedure for patients with GGO-containing clinical stage T1a-T1b IADCs.

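### The only test named for RFS is a two-sided log-rank test of equality, which does not match the one-sided 5%, 5-point non-inferiority design and cannot establish non-inferiority

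*Protocol article*

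**What the plan says.** **Endpoint** (Study endpoints, first sentence): "The primary endpoint is 5-year recurrence-free survival (RFS), calculated from the date of surgery to the date of cancer recurrence or patient death". Patients without an event count up to their last follow-up.

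**Design** (Sample size calculation): the expected 5-year RFS is 91%. The section continues "With a one-sided alpha error of 5% and at least 80% power", and then "a non-inferiority margin of 5% along with a drop-out rate of 5" per cent, to reach 1024 patients.

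**Analysis** (Statistical analysis): a two-sided 0.05 level marks a statistical difference. Comparisons of RFS and OS "are all estimated by Kaplan-Meier method and testified by the two-side Log-rank test". A Cox model supplies hazard ratios for both endpoints. ITT and per-protocol analyses are planned. The section does not mention the 5% margin, the one-sided level or any confidence limit.

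**Conclusion** (Abstract, Discussions; repeated in Conclusions): the recommendation is conditional. "If the primary endpoint shows at least non-inferiority in 5-year RFS of segmentectomy to lobectomy", segmentectomy can be offered as an alternative. How non-inferiority is to be judged is not stated.

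**The concern.** The design and the analysis answer different questions. The design sets out to reject the hypothesis that segmentectomy is worse by 5 points or more at 5 years, with a 5% one-sided error. The named test can only reject the hypothesis that the two RFS curves are equal. A significant result says the curves differ. A non-significant one says only that a difference was not demonstrated. Neither outcome says whether a 5-point deficit has been excluded.

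The Cox hazard ratio does not close the gap as described, because the article attaches no confidence limit to it and never converts 5 points into a ratio.

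At stake is the trial's central conclusion. If the margin-based rule is not fixed, the choice of scale, confidence level and criterion stays open until results are known. One possible choice, treating absence of significance as non-inferiority, would not hold the 5% error the trial was sized for.

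**Working it through.** **Inputs from the article:** expected 5-year RFS 91%; margin 5%, read as 5 points (91% versus 86%); one-sided alpha 5%; power at least 80%; dropout 5%; 1024 patients, 1:1; follow-up to year 5.

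**Assumptions added here:** exponential RFS; dropouts contribute nothing, so 1024 × 0.95 ≈ 972 analysable, 486 per arm.

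**1. The plan's own figure.** No formula is named. The closest match that uses all stated inputs is a time-to-event calculation.
- Hazard-ratio margin: ln(0.86)/ln(0.91) = 1.599, with ln(1.599) = 0.4695.
- Events: 4 × (1.645 + 0.842)² / 0.4695² ≈ 112.2, so 113.
- Mean event probability: (0.09 + 0.14)/2 = 0.115. Patients: 113/0.115 ≈ 983. With dropout: 983/0.95 ≈ 1035, which is 1.1% above 1024.
- A binomial non-inferiority calculation with 91% in both arms gives 812, or 855 with dropout.

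Both are non-inferiority calculations that use the margin.

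**2. What the log-rank test does when the truth is on the margin (91% versus 86%).**
- Events: 972 × 0.115 ≈ 112.
- Expected z: 0.4695 × √(112/4) ≈ 2.48.
- P(two-sided p > 0.05) ≈ Φ(1.96 - 2.48) ≈ 0.30. With all 1024 analysable it is 0.28.
- A simulation of 4,000 trials gave 30% non-significant. A margin test at one-sided 5% declared non-inferiority in 4.9% of the same trials.

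**3. Beyond the margin (91% versus 85%).** The log-rank test is still non-significant in 16-17% of trials.

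**4. One concrete result** (binomial approximation, 486 per arm). Suppose 91% versus 88% is observed.
- SE = √[(0.91 × 0.09 + 0.88 × 0.12)/486] = 0.0196.
- z = 0.03/0.0196 = 1.53, two-sided p = 0.13.
- Upper 90% limit of the deficit: 3.0 + 1.645 × 1.96 = 6.2 points.

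The difference is not significant, and a 5-point deficit is not excluded.

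**5. Both arms truly 91%.** In the simulation about 13% of trials were non-significant on log-rank yet failed the margin test. The two criteria therefore disagree even when the procedures are equivalent.

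**6. Power of a margin-based test at one-sided 5%.**
- Difference scale, 91% in both arms, 486 per arm: SE = √(2 × 0.91 × 0.09/486) = 0.01836; Φ(0.05/0.01836 - 1.645) = Φ(1.08) ≈ 86%.
- Hazard-ratio scale with the 112 events of step 1: Φ(2.48 - 1.645) ≈ 80%.
- Hazard-ratio scale if both arms really have 91% and follow-up stops at 5 years: 972 × 0.09 ≈ 87 events; Φ(0.4695 × √(87/4) - 1.645) ≈ Φ(0.55) ≈ 71%.

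**The case against.** The strongest reply is that this is a condensed article and the analysis plan is not shown. The article fixes the margin, the one-sided alpha and the expected RFS. It plans Kaplan-Meier and Cox estimates in ITT and per-protocol sets. Either estimate could carry a margin test once a confidence limit is attached, so it would be wrong to say that the planned estimates could never support non-inferiority. That stands. It does not remove the point, because the article is not silent on the test. It names one, with its sidedness and level, and that test contradicts the design in the preceding section. An analysis plan with a margin-based rule would itself depart from this text.

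A reader might also infer more than the article supports:
- **That p ≥ 0.05 will be taken as non-inferiority.** The article states no such rule. The 30% in step 2 is conditional on that reading and does not describe a declared procedure.
- **That the log-rank test is designated the primary analysis.** It is not labelled so. It is the only test named for RFS, in a sentence that also covers OS.
- **That the plan rewards losing events.** This too depends on the unstated rule.

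Finally, comparing whole curves is not a fault in itself. The stated sample size lies nearer to a hazard-ratio margin of about 1.60 (1035) than to a binomial difference (855). That does not prove which method was used, but a hazard-ratio test would be as legitimate as a 5-year difference.

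**Conclusion.** The mismatch is real and concerns the primary endpoint. The design is one-sided at 5% with a 5-point margin, while the only named test is a two-sided test of equality that does not use the margin and so cannot establish the non-inferiority on which the recommendation depends. This follows from the text and needs no numerical assumption.

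The size is conditional. If non-significance were taken as non-inferiority, false acceptance at the margin would be about 30%, roughly six times the designed 5%. That figure assumes 91% versus 86%, exponential RFS, about 486 analysable per arm and 5-year follow-up. It ranges from 28% with all 1024 analysable to 30% with 972. Confidence is high for the mismatch. How the investigators would read a non-significant result cannot be judged from the article. The point must be fixed, because it bears on the central conclusion and the remedy is cheap.

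**What to change.** Reconcile the Statistical analysis section with the Sample size calculation by stating one primary margin-based test at the one-sided 5% level. Choose one scale before any RFS results are seen:

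- **Difference:** declare non-inferiority if the lower limit of the two-sided 90% confidence interval for the Kaplan-Meier 5-year RFS difference (segmentectomy minus lobectomy, Greenwood standard errors) is above -5 points; or
- **Hazard ratio:** declare non-inferiority if the upper limit of the two-sided 90% confidence interval for the Cox hazard ratio (segmentectomy versus lobectomy) is below ln(0.86)/ln(0.91) = 1.60.

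Apply the rule in the ITT and per-protocol sets already planned. Keep the two-sided log-rank test for superiority, after non-inferiority is met.

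The cost is protocol and analysis-plan wording, with no extra data. Stating the rule needs no change to the 1024 patients. Power is about 86% on the difference scale and about 80% on the hazard-ratio scale with 112 events. Weigh one thing when choosing: if both arms truly have 91% and follow-up ends at 5 years, only about 87 events arise and hazard-ratio power is nearer 71%.
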